### 2.2. Recruitment and Informed Consent

The study involves 35 patients with PE who wish to participate in a three-month physiotherapy program. Before the study begins, parents or guardians will be informed both verbally and in writing about all the details and milestones of the study.

The study is conducted in accordance with the Declaration of Helsinki and has been approved by the Ethics Committee of the “Victor Babeș” University of Medicine and Pharmacy in Timișoara, NO. 12/10.02.2025.

#### 2.2.1. Inclusion Criteria

The requirements for participation in the study are as follows: the subject diagnosed with PE must be a child or adolescent, not older than 18 years, and must exhibit a clinically visible appearance with a mild anterior chest concavity, confirmed by a CT scan using the Haller index, which should be less than 3.25. This index represents the ratio between the transverse diameter of the chest and its anteroposterior diameter at the point where the deformity is most pronounced. Lastly, participants must be available for the necessary evaluations at both the start and end of the study. [3]. Severity is usually quantified by the Haller Index and the Correction Index, both widely accepted for guiding treatment [3]. The Haller Index was developed in the 1980s and is based on CT images of the chest, calculated by dividing the transverse diameter by the sagittal diameter of the rib cage [16]. The Correction Index is a more recent and more precise tool for assessing the severity of PE, calculated by dividing the minimum distance between the posterior sternum and anterior spine by the maximum distance between the anterior spine and the most anterior portion of the chest [17].

#### 2.2.2. Exclusion Criteria

Subjects will be excluded from the study if they have had less than 3 months since any surgery, are recalcitrant, unable to concentrate, refuse cooperation, or are unwilling to follow the daily exercise plan. Children with mild scoliosis associated with the condition are eligible; they are evaluated during the initial consultation (clinical, paraclinical, and functional). Regarding associated pathology, the study participant must be free of neurological problems, epilepsy, moderate or severe scoliosis, or genetic syndromes.

#### 2.2.3. Discontinuing Criteria

Any subject who does not follow, interrupt, or deviate from the daily exercise program will be excluded from the study. Patients are also excluded if, during the study period, they suffer any injury that may affect their ability to adhere to the physiotherapy program.

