## 2. Materials and Methods

This protocol study aims to evaluate a group of patients with PE treated with physical therapy to highlight the importance of physical exercise in managing this condition. Respiratory rehabilitation helps restore muscle elasticity and corrects the overall body posture. This study is conducted at the Emergency Clinical Hospital for Children in Timișoara, within the Medical Rehabilitation Department, from March 2025 to July 2026.

This article outlines the study protocol for assessing the efficacy and safety of a structured physiotherapy program in children with pectus excavatum; we also note that this is a prospective study. The main objective is to evaluate the effect of the physiotherapy program on respiratory function and body posture after three months of treatment, while secondary objectives include safety monitoring, assessment of postural improvements, and analysis of quality-of-life outcomes. By publishing this protocol, we aim to promote transparency in research methodology and provide a clear framework for the upcoming clinical study, the results of which will be shared in a later article.

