### 2.3. Exercise Program

Following the parameters obtained during the initial assessment, the physiotherapist will develop a personalized exercise plan tailored to the patient’s needs.

At this stage, the physiotherapy program is designed and learned under the guidance of the physical therapist (2 weeks, 5 sessions per week, 60 min per session) and continued at home daily for three months. During the 10 physiotherapy sessions with the specialist, the patient carefully and correctly learns the exercises to perform at home in the next phase.

The objectives of the exercise program are to correct upper trunk posture, straighten the spinal column, increase mobility, re-educate muscles (by strengthening paravertebral muscles and relaxing muscles in the anterior thoracic area), and prevent or correct secondary axial deviations. Additionally, it aims to improve respiratory function and properly manage breathing during exercise.

The program includes exercises for spinal and rib cage mobility, exercises for toning the extensor trunk muscles (focusing on strengthening the back muscles and relaxing or stretching the front trunk muscles), respiratory re-education exercises, and exercises for stability re-education. To understand the program, Table 1 provides a detailed description of the exercises specifically designed by the authors in a potential work plan.

Proposed exercise plan for patients with PE and secondary axial deviations:

**Table 1 life-15-01624-t001:** Proposed exercise plan for patients with PE.

	Medical Rehabilitation Center	Home Exercise
Exercise Description	Number of Repetitions Week 1–2	Number of Repetitions Week 3–12
***Exercise 1:*** Patient sitting on a Bobath ball, feet on the ground, knee and hip joint, upper limbs placed behind the cervical spine with palms in contact with the cervical spine and arms close to the ear. The patient brings the arms back with an inhale, holds the position for 3–5 s and returns to the starting position with an exhale. (Figure 1a,b)	10 repetitions × 2 sets	10 repetitions × 3 sets
***Exercise 2:*** The patient on the Bobath ball, seated as in the previous exercise, positions the hands under the mandible parallel to the ground, and brings the arms backwards with double extension while inhaling, and then forward while exhaling.	10 repetitions × 2 sets	10 repetitions × 3 sets

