### 2.4. Measurements

In the first stage, we conduct investigations to establish the patient’s sample, and the physiotherapist designs a personalized physiotherapy program. This is followed by the second stage, where the physiotherapy program is carried out and learned under the guidance of the specialist. The final stage involves re-evaluating the patient after completing the physiotherapy program and drawing conclusions from the study.

Each parameter will be reviewed by the investigators, documented in an Excel file, and then their correlation will be analyzed using a statistical program.

In the initial phase after establishing the two samples, evaluation of each subject begins as follows: myotonometric assessment of the involved muscles (Trapezius muscle with all three fascicles, Pectoralis Major muscle), on both the left and right sides, along with cardiopulmonary exercise testing (CPET), postural analysis (GaitOn), and static balance measurement (stabilometry-PoData), using non-invasive tests.

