### 2.5. Statistical Analysis

Statistics will be performed using GraphPad Prism 5.0 for Windows. The descriptive statistics will be computed for all variables (mean and standard deviation). Before statistical applications, the normal distribution of values will be verified by the D’Agostino-Pearson normality test. The intragroup data (analyzed parameters at baseline and after the physical exercise program) will be compared with the paired *t*-test.

For the myotonometry, frequency, stiffness, decrement, stress relaxation time and creep of the trapezius and major pectoralis will be compared before and after the 3-month physical exercise program. VE and VO_2max_ will be analyzed at baseline and after the physical exercise program. Paired *t*-tests will be used to compare the intragroup data of the postural stability parameters (stabilometry data in the different testing situations). GaitOn postural analysis parameters will be measured before and after the 3-month physical exercise program.

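### Leaving the exercise programme is treated as leaving the study, so the before-after change is estimated only in adherent completers, and the injury exclusion conflicts with the safety objective

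*Protocol article*

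**What the plan says.** Section 2.2.3 (Discontinuing Criteria) has two rules. The first concerns adherence: "Any subject who does not follow, interrupt, or deviate from the daily exercise program will be excluded from the study". The intended meaning is clear despite the grammar: a child who does not follow the programme, interrupts it or departs from it is removed. No adherence threshold is given. The second concerns injury: "Patients are also excluded if, during the study period, they suffer any injury that may affect their ability to adhere to the physiotherapy program". It is limited to injuries that may affect adherence, but not by cause, so an injury from the exercises themselves falls under it.

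The programme to which these rules apply is taught in 10 supervised sessions and then "continued at home daily for three months" (section 2.3). On the final assessment, section 2.4 says: "The final stage involves re-evaluating the patient after completing the physiotherapy program and drawing conclusions from the study". On the analysis, section 2.5 says: "The intragroup data (analyzed parameters at baseline and after the physical exercise program) will be compared with the paired" t-test.

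Section 2 describes the purpose as "assessing the efficacy and safety of a structured physiotherapy program in children with pectus excavatum". It continues: "The main objective is to evaluate the effect of the physiotherapy program on respiratory function and body posture after three months of treatment". It adds that "secondary objectives include safety monitoring, assessment of postural improvements, and analysis of quality-of-life outcomes".

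Section 2.1 requires at least 35 patients, and section 2.2 enrols 35.

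**The concern.** The exclusion is from the study, not only from the exercises, and it is triggered by events after baseline. A child who feels no benefit, finds the exercises hard or is hurt by them is plausibly more likely to stop. If so, the children who remain have changed more favourably than all those who began. In a controlled trial a comparator might share part of such selection. Here the planned comparison is within one group, so the selection passes directly into the estimated change and cannot be separated from the effect of the programme.

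Two further things are at stake. The main objective and the conclusions concern physiotherapy for children with pectus excavatum, whereas the result would concern those who kept to a daily programme for about three months. And a study that names safety as an aim removes the children whose injuries say most about safety.

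**Working it through.** **1. Who can be analysed.** A paired test needs a baseline and a final value. The final value is taken after completion of the programme (2.4). Children who depart from the programme, or have an injury that may affect adherence, are out of the study before then (2.2.3). No section keeps them in follow-up or in an analysis. The set that remains is adherent completers.

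**2. The plan's own figure.** Inputs from 2.1: effect size 0.5, α = 0.05, power 0.8, Wilcoxon signed-rank test for matched pairs. Sidedness is not stated; two-sided is taken. The power is that of a noncentral t with effective size m = n × 3/π (the asymptotic relative efficiency under a normal parent), m − 1 degrees of freedom and noncentrality 0.5√m. At n = 35, m = 33.4, noncentrality is 2.89 and power is 0.801. So 35 reproduces as the smallest sufficient n. A two-sided paired t-test needs 34 (power 0.808) and has power 0.820 at 35. Neither leaves room for more than about one exclusion.

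**3. Loss of precision.** The documents give no exclusion rate, so a range is assumed, with 35 enrolled, no replacement and completers rounded down:

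| Excluded | Completers | Power, Wilcoxon | Power, paired t | Enrolment needed to keep 35 |
|---|---|---|---|---|
| 10% | 31 | 0.75 | 0.77 | 39 |
| 20% | 28 | 0.70 | 0.72 | 44 |
| 30% | 24 | 0.63 | 0.65 | 50 |

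The last column is 35/(1 − proportion excluded), rounded up.

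**4. Selection.** Assumptions, none from the documents: individual change (SD 1, mean δ) and adherence are bivariate normal with correlation r of 0.3 or 0.5, and the least adherent proportion q is excluded. With a = Φ⁻¹(q):

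- λ = φ(a)/(1 − q) is the mean adherence of those retained, and v = 1 + aλ − λ² its variance.
- Mean change in completers = δ + rλ; SD = √(1 − r² + r²v).
- Completer dz = (δ + rλ)/√(1 − r² + r²v).

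For q = 0.20: a = −0.842, λ = 0.350, v = 0.583. With r = 0.5 and δ = 0, dz = 0.175/0.946 = 0.185. With δ = 0.30, dz = 0.475/0.946 = 0.50.

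With a true mean change of zero, and rejection rates from the noncentral t at n = 32, 28 and 25 (31.5 and 24.5 rounded up):

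| Excluded | dz, r = 0.3 | dz, r = 0.5 | Two-sided error at nominal 5% |
|---|---|---|---|
| 10% | 0.06 | 0.10 | 6.2 to 8.6% |
| 20% | 0.11 | 0.18 | 8.5 to 15.7% |
| 30% | 0.15 | 0.27 | 11.3 to 24.8% |

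Rounding the completers down instead lowers the error by at most about one percentage point.

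**5. The same point without the normal model.** Suppose completers change by 0.50 SD and excluded children by 0 to 0.25 SD. With 20% excluded, the mean over all who start is 0.8 × 0.50 + 0.2 × (0 to 0.25) = 0.40 to 0.45. The completer analysis still reports 0.50.

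**6. Safety.** Section 2 names safety as an aim and a secondary objective. Section 2.2.3 removes children because of injury. The two sections do not say how an injury that leads to exclusion reaches the safety result.

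**The case against.** - **An adherent-only effect is a legitimate quantity.** This stands if it is labelled as such. If adherence correlates with change because doing more exercise works, the completer result describes what the programme does when followed. The inflated error rates need a correlation at zero mean change, for instance because children who see no improvement stop. They are illustrative. The objectives, however, are not worded as an effect in adherers.
- **The full protocol or analysis plan may define an adherence threshold or analysis set.** It may soften how strictly a deviation is judged. But the article states a rule of exclusion from the study, and a later document retaining these children would contradict it.
- **Harms.** A reader might infer that injuries vanish from the safety data. The text does not support that. It does not say that injuries go unrecorded or that collected data are discarded, recording of adverse events may be described elsewhere, and only injuries that may affect adherence lead to exclusion. What stands is a conflict between sections to be reconciled.
- **The sample may be topped up.** Section 2.1 says at least 35 and replacement is not ruled out. Replacement would restore the number but not remove the selection.
- **There may be a comparator.** The Discussion calls the study randomised and section 2.4 mentions two samples. Sections 2.1, 2.2 and 2.5 describe one group and within-group tests only, so no comparator is available to absorb the selection.
- **Without a control arm, growth and practice effects remain anyway.** True, and this fix does not address them. It is no reason to add a further avoidable bias.

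**Conclusion.** The point holds. Section 2.2.3 conflates stopping the exercises with leaving the study. Together with 2.4 and 2.5 it restricts the before-after estimate to a set selected after baseline. The direction, too favourable for all who start, is likely but rests on the assumption that children doing less well are the ones who leave. The size cannot be fixed from the documents. For a correlation of 0.3 to 0.5 and 10 to 30% excluded, the bias at zero true change is about 0.06 to 0.27 in dz and the error about 6 to 25%. At the stronger correlation with 20% excluded, a true dz of 0.30 reads as 0.50, which is the planning effect. The loss of power to about 0.70 to 0.72 at 20% exclusion assumes no replacement. The injury rule and the safety objective must be reconciled; loss of harms data is not shown. This should be settled while final assessments can still be made, since those not made cannot be recovered.

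**What to change.** **Section 2.2.3.** State that stopping, interrupting or deviating from the programme, or being injured, neither ends study participation nor removes data already collected. Seek the three-month assessment for everyone who started, where assessment is possible. Whether an injured child continues exercising or undergoes the treadmill test stays a matter of clinical judgement, outside this wording.

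**Section 2.5.** Make the main analysis all starters with baseline and final values, regardless of adherence. Report numbers and reasons for loss for all enrolled. Present the adherent-only result as supportive and labelled. Report all injuries as safety outcomes, including those that lead to stopping the exercises.

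**Cost.** A few sentences, plus some tracking of children who have stopped. Final assessments for 35 are already foreseen, but the article ties them to completing the programme, so inviting non-adherers is extra effort. The estimated effect will probably be smaller. Selection is reduced, not eliminated, because children who miss the final visit still drop out of the paired analysis; the reported reasons for loss let readers judge what remains.

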#### 2.4.2. Cardiopulmonary Exercise Testing (CPET)

Assessment of cardiopulmonary condition will be performed with the BTL-CPET device, which uses glue-wired electrodes that are attached by a cable to a portable EKG device mounted around the patient’s abdomen [20].

Blood pressure should be measured at the beginning and at the end of the test. Alternatively, a blood pressure cuff may be attached to the patient’s arm. Additionally, a pulse oximeter will be worn on the patient’s finger to monitor tissue oxygen levels and heart rate.

A mask that attaches to the head with a rubber band is used for lung testing. It must be sealed so the person breathes only through the opening in the mask. A cylinder is inserted into the hole in the mask and connected by wires to an air filter. The filter provides data on the amount of oxygen inhaled and the amount of carbon dioxide exhaled.

Once the preparations are complete, the patient is asked to step onto the treadmill to start testing. This begins with a 3 min warm-up period during which the patient is asked to walk. After the warm-up, the actual testing begins. Each level has a specific incline and speed, which increase gradually during the test (Figure 10).

The study uses the modified Bruce Protocol, which starts at a speed of 1.7 mph and a 0% incline. The second and third stages maintain the same speed, but the slope increases by 5% in each stage. Each subsequent stage increases in speed by 1.12 to 1.28 km/h and in incline by 2%. The test lasts approximately 10 to 13 min, followed by a 3 min recovery period [21].

With cardiopulmonary exercise testing, we gather data on the body’s response to both maximal and submaximal exercise by recording cardiac parameters (electrocardiogram) and respiratory parameters. Depending on the respiratory gases, we calculate VE and VO_2max_ [22].

Endurance capacity indicators include maximal oxygen consumption (VO_2_) and ventilation thresholds (VT1 and VT2). Additionally, anaerobic capacity, movement economy, and mechanical efficiency can also be assessed through gas exchange measurements, while cardiopulmonary exercise testing helps define exercise intensity zones.

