## 4. Discussion

The study will be randomized and will examine the characteristics of the trapezius and pectoralis major muscles, respiratory function, stability, and overall posture in children and adolescents with PE before and after a tailored physical therapy program lasting three months. The assessment of study participants will include four different testing methods: myotonometry, cardiopulmonary exercise testing (CPET), posture evaluation, and static balance analysis.

An excessively high position in the upper chest area may cause PE, and the pectoralis major muscle has a biomechanical role in lifting the sternum [25]. Consequently, the main hypothesis of this investigation will focus on assessing the tone of the pectoralis major and trapezius muscles, as well as examining any recorded discrepancies that might contribute to this condition. The study will explore changes in length, elasticity, muscle tone, and relaxation in muscles potentially involved in the development of the pathology through a non-invasive measurement method: myotonometry. No studies have been found in the literature that evaluate the properties of muscles involved in the development of PE. However, some evidence links thoracic kyphosis with this condition [6], prompting an analysis of the literature’s reported changes and a comparison with the findings of this study. Thoracic kyphosis appears as limited mobility of the thoracic spine caused by alterations in both non-contractile and contractile tissues [26].

Therefore, in a study conducted by Yeo et al., muscle tone was evaluated in the upper trapezius and pectoralis major muscles of patients with thoracic kyphosis using MyotonPro^®^ (Myoton AS, Tallinn, Estonia). Variations in the examined parameters were observed [27]. The measurement technique used in this study is similar to that in our research, with the MyotonPRO^®^ tip positioned vertically at the midpoint of the subjects’ upper trapezius and pectoralis major muscles.

The CPET evaluation of the study participants will assess the effect of sternal deformity on cardiopulmonary function and compare the results with those reported in existing literature.

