Davi DE Podestá Haje et al. also highlight the importance of physical activity in children and adolescents with mild to moderate PE. A study involving participants who performed targeted exercises to strengthen the anterior chest muscles at least five times a week, under the supervision of a physical therapist and with controlled breathing, considered various factors, including patient age and compliance with the program. The results demonstrated the exercises’ effectiveness in correcting or partially correcting pectus excavatum, especially when therapy began early in cases of milder and more flexible deformities. The exercise regimen used by participants included simultaneous resistance-free abduction and extension of the upper limbs, trunk extension while lying down, push-ups, sit-ups, and blowing up a balloon for 10 min [39].

In a 2020 study, Nuray Alaca et al. recommended kinetotherapy, which includes cardiopulmonary exercises and chest muscle toning, for patients with pectus excavatum. The physical therapy program involved breathing exercises for each lung lobe, upper and middle/lower diaphragmatic lateral rib breathing exercises, and exercises for the musculoskeletal system that included postural awareness, trunk mobilization and manipulation, stretching, strengthening, and additional aerobic exercises [11].

The proposed exercise program, although similar to those described in previous studies and detailed in the Materials and Methods section, is unique because it is performed daily for three months and tailored individually based on parameters identified during the initial assessments.

The effect of the three-month exercise program on children and adolescents with PE will be studied in relation to deformity progression. The evaluated parameters will be correlated, and the findings compared with existing research to aid in developing an assessment and rehabilitation protocol for these patients.

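### Safety and quality of life are stated aims, but children with adherence-limiting injuries leave the study with no stated place in a safety count, and no listed assessment measures quality of life

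*Protocol article*

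**What the plan says.** The article describes its purpose in section 2 as "assessing the efficacy and safety of a structured physiotherapy program in children with pectus excavatum". It adds that "secondary objectives include safety monitoring, assessment of postural improvements, and analysis of quality-of-life outcomes".

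Section 2.2.3 (Discontinuing Criteria) has two removal rules. On adherence: "Any subject who does not follow, interrupt, or deviate from the daily exercise program will be excluded from the study". On injury: "Patients are also excluded if, during the study period, they suffer any injury that may affect their ability to adhere" to the physiotherapy programme. Neither rule refers to the cause of the injury or the reason for the interruption.

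Section 4 lists the measurements: "The assessment of study participants will include four different testing methods: myotonometry, cardiopulmonary exercise testing (CPET), posture evaluation, and static balance analysis". The Abstract, the end of section 1 and section 2.4 name the same four. Section 2.5 lists the variables to be compared before and after the programme, all of them outputs of these devices. Section 3 expects changes in the same four. Section 2.4.2 also describes ECG, pulse oximetry and blood pressure around the treadmill test: "Blood pressure should be measured at the beginning and at the end of the test".

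Late in section 4 the article says that the effect of the programme "will be studied in relation to deformity progression".

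**The concern.** After two weeks of supervised teaching, the children exercise daily at home. Injuries or pain that make a child stop are among the harms that a safety objective for such a programme would need to count. The two rules in section 2.2.3 remove these children from the study, and no section says that they still count for safety. A statement that no such injuries occurred could then come from a sample selected for not having had them.

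The quality-of-life problem is simpler. An objective is announced, but no listed measurement could supply its data. At stake are one part of the declared purpose (safety) and one secondary objective. The main objective, respiratory function and posture, is not questioned here.

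**Working it through.** **1. The denominator.** Section 2.1 gives effect size 0.5, α = 0.05, power 0.8 and the matched-pairs signed-rank test, with at least 35 patients. Using the normal-parent asymptotic relative efficiency 3/π, the effective size is 35 × 3/π = 33.42 and the noncentrality is 0.5 × √33.42 = 2.89. Two-sided power from the noncentral t is 0.8007, and 35 is the smallest number that reaches 0.80. The figure of 35 reproduces and is not in dispute. It is used below as the number enrolled, as in section 2.2.

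**2. Objectives set against measurements.**

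| Stated aim (section 2) | Source of data in the article | Gap |
|---|---|---|
| Safety of the programme | ECG, oximetry and blood pressure in section 2.4.2 | These cover the treadmill test, not three months of exercise; section 2.5 lists no safety variable |
| Quality of life | None of the four assessments; no variable in section 2.5; not mentioned in section 3 | No instrument and no variable |
| Posture | GaitOn (section 2.4.4), listed in section 2.5 | None on this point |

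**3. What the injury rule does to a count.** Let x of n enrolled children have an injury that may affect adherence. Counted over all enrolled, the rate is x/n. Under section 2.2.3 all x leave, so among the n − x who remain the count of such injuries is 0 whatever x was. This follows from the rule alone. Injuries that do not threaten adherence are unaffected and can still be counted.

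**4. How likely the rule is to matter.** The documents give no injury rate, so a range is assumed. With n = 35, the expected number is 35p and P(at least one) = 1 − (1 − p)^35.

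| Assumed rate p | Expected injuries | P(at least one) | Count among those retained |
|---|---|---|---|
| 2% | 0.7 | 51% | 0 |
| 5% | 1.75 | 83% | 0 |
| 10% | 3.5 | 97.5% | 0 |
| 20% | 7 | >99.9% | 0 |

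**5. One illustration.** Take x = 3, an assumed figure. The exact (Clopper-Pearson) limits are the 2.5% quantile of Beta(x, n − x + 1) and the 97.5% quantile of Beta(x + 1, n − x).

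- All enrolled: 3/35 = 8.6%, 95% CI 1.8% to 23.1%.
- Retained only: 0/32 = 0%, with upper limit 1 − 0.025^(1/32) = 10.9%. The one-sided 95% limit is 1 − 0.05^(1/32) = 8.9%.

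The second line looks reassuring only because the three children are no longer in it.

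**The case against.** The strongest reply is that section 2.2.3 says who leaves the study, not that the injury goes unrecorded. Staff must notice an injury in order to apply the rule. An article condenses a fuller protocol, which commonly holds the adverse-event procedures and the definition of the safety population. This stands in part. A reader might infer that the safety result is certain to be wrong, and the documents do not support that. The bias arises if safety is reported on the children who remain. That is the natural reading of exclusion from the study, but it is not stated. What survives is that the article fixes an explicit removal rule that pulls against its own stated aim, and nothing in it reconciles the two.

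A reader might also infer that every injured child is removed. That is too strong, since only injuries that may affect adherence trigger the rule.

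It can be said too that the four methods are not declared exhaustive: "The assessment of study participants will include four different testing methods". Entry also involves a CT-based Haller index and an initial consultation. For quality of life this carries little weight, because the same four methods recur throughout and sections 2.5 and 3 omit quality of life as well.

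Finally, a reader might take deformity progression to be a further objective without data. It is one loose sentence in the Discussion and is not among the objectives in section 2. Section 2.2.1 uses the Haller index as an entry criterion and does not say whether it is repeated, so measurement at entry only would be an inference from silence.

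**Conclusion.** The point holds on two counts of unequal strength.

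- **Quality of life (high confidence).** The objective cannot be answered with the assessments and variables listed.
- **Safety (moderate confidence).** If safety is reported on retained children, adherence-limiting injuries are zero by construction and the conclusion is biased in favour of the programme. The direction is clear. The size cannot be computed, because no injury rate is given; 3 of 35 against 0 of 32 shows the mechanism and does not estimate this trial's bias. The conclusion assumes that removed children are left out of the safety report, and a fuller protocol that records and counts these events would remove the bias.

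This should be fixed. It concerns secondary aims and leaves the main paired comparison and the sample size of 35 untouched.

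**What to change.** 1. Reconcile section 2.2.3 with section 2 by separating discontinuation of the programme from removal from the study data. This requires no change to any clinical rule about who stops or when.
2. Record each injury or other adverse event, including those that lead to discontinuation, with its relation to the programme. Report counts over all enrolled children with exact 95% confidence intervals.
3. For quality of life, either add a short validated paediatric questionnaire at the two existing assessment visits and list its score in section 2.5, or delete the objective.
4. Delete or reword the remark on deformity progression in section 4, unless a repeated deformity measure is already planned.

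The cost is one amended paragraph and an adverse-event entry in the existing data file. A questionnaire would take a few minutes per visit; deleting the objective costs nothing. No extra visit is needed.
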